## Abstract

**Background:**

Within the field of plastic surgery, free tissue transfer is common practice for knee and lower leg defects. Usually, after such free flap reconstruction, patients undergo a dangling protocol in the postoperative phase. A dangling protocol is designed to gradually subject the free flap to increased venous pressure resulting from gravitational forces. Worldwide there are multiple variations of dangling protocols. However, there is no evidence available in the literature that supports the use of a dangling protocol.

**Methods:**

This is a multicenter randomized controlled trial that includes patients with a free flap lower leg reconstruction. The primary outcome is to assess whether a no-dangling protocol is not inferior to a dangling protocol, in terms of proportion of partial flap loss, 6 months after surgery. Secondary objectives are to identify differences in major and minor complications, length of stay, and costs, and to objectify blood gaseous changes during dangling. Furthermore, at 2 years we will assess difference in physical function, infection rates, and osseous union rates.

**Discussion:**

The primary outcome of this study will give a more decisive answer to the question of whether a dangling protocol is necessary after a free flap reconstruction of the lower leg. The secondary outcomes of this study will provide a better insight into the physical functions, infection rates, and union rates in these patients.

**Trial registration:**

Central Committee on Research Involving Human Subjects (CCMO), NL63146.041.17. Registered on 11 July 2018. Netherlands Trial Register, NTR7545. Registered on 10 October 2018.

**Electronic supplementary material:**

The online version of this article (10.1186/s13063-019-3665-0) contains supplementary material, which is available to authorized users.

## Background

Within the field of plastic surgery, free tissue transfer is common practice. In knee and lower leg defects due to trauma, oncological resection, or chronic infection, adequate soft tissue coverage of bony structures is imminent. In case of insufficient bony coverage, a muscle or fasciocutaneous (skin, fat, and fascia) free tissue transplantation is performed. This is a microsurgical operation in which distant body tissue is transplanted to the defect. However, there is great diversity in the postoperative care for patients with a lower leg reconstruction. Usually, after such free flap reconstruction, patients undergo a dangling protocol in the postoperative phase. During this dangling protocol, the patients hang the reconstructed lower leg from the side of the bed in order to gradually subject the free flap to increased venous pressure resulting from gravitational forces. Worldwide there are multiple variations of dangling protocols. The starting point, frequency, and duration vary widely; whereas some start the dangling protocol as early as on the second postoperative day (POD), others wait until the fourth postoperative week [1–3]. Some report not to use dangling as a standard procedure at all [1], and some use it only in select cases [2]. In general, the dangling protocol is performed in a hospital setting. Although not supported by any evidence, dangling protocols are designed to decrease the risk of postoperative complications such as partial or total flap necrosis. These protocols usually extend hospital stay, resulting in higher costs.

Jokuszies et al. [4] and Neubert et al. [5] performed the only two known randomized controlled trials in this patient group. They compared an early start of the dangling protocol on POD 3 to the more standard starting point on POD 7. Both studies showed that the combined wrapping and dangling procedure can safely be started at POD 3. It must be noted that the patients included in these studies were for the most part the same group of patients. Furthermore, the numbers of patients in both studies were small (31 and 49), resulting in an underpowered study [4, 5]. McGhee et al. published a systematic review comparing an early dangling protocol to a late dangling protocol [6]. They found eight relevant articles, including the studies performed by Jokuszies et al. [4] and Neubert et al. [5]. Based on the currently available literature, they concluded that an early dangling protocol can be safely used. A more recent systematic review by Soteropulos et al. came to a similar conclusion [7].

Both systematic reviews are calling for a larger randomized controlled trial. Moreover, whether or not to dangle at all is an intriguing question. We hypothesize that the free flap as a result of flap ingrowth regains its venoarterial response and will develop increased venous outflow over time. We believe that this is independent of a dangling protocol. Therefore, we designed a study protocol for a large multicenter randomized controlled trial, which we present in this article.

### Objectives

The primary objective is to assess whether a no-dangling protocol is not inferior to a dangling protocol. Our primary outcome is measured in terms of proportion of patients who experienced partial flap loss which did not require another free flap procedure. Total follow-up for our primary objective is 6 months. Based on a rate of partial flap loss of 6%, we decided that an absolute increase in incidence of 12% would be clinically significant. We will calculate the absolute risk differences in incidence of partial flap loss (major and minor combined) between groups.

We also have the following secondary objectives:
We hypothesize that there is no difference in one or more major complications at 6 months.We would like to objectify the gaseous changes within the free flap during the dangling protocol in a select group of patients.We will measure the physical functions at 3 and 6 months and at 1, 1.5, and 2 years with the Patient-Reported Outcomes Measurement Information System (PROMIS) physical function, EuroQol five dimensions (EQ-5D), and visual analog scale (VAS) questionnaires.We hypothesize that there is no difference in the number of patients experiencing one or more minor complications at 3 and 6 months postoperatively.We will investigate whether there is a difference in the length of hospital stay between the two groups and perform a costs analysis.We will investigate infection rates and osseous union rates with a follow-up of 2 years.

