### Study parameters

As our primary study parameter we will investigate whether there is a significant increase in the incidence of partial flap loss in patients who did not undergo a dangling protocol (group B) versus patients who did undergo a dangling protocol (group A). We defined complete flap necrosis, partial flap necrosis (if a revision surgery with a second free flap is necessary), and pulmonary embolism as major complications. Screening for pulmonary embolism will only be performed if there is a clinical suspicion of a pulmonary embolism. Partial flap loss is defined as a minor complication if no secondary free flap is needed or as a major complication if a secondary free flap was needed. Wound dehiscence, wound infection, failure of skin graft ingrowth on the free flap, and hematoma for which a surgical exploration was needed were defined as minor complications.

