### Statistical analysis

As the primary hypothesis we will calculate the absolute risk differences in incidence of partial flap loss (major and minor combined) between groups. If the upper limit of the 95% CI falls within 12%, we regard this as a non-inferiority difference.

The secondary hypotheses will be tested for superiority: absolute risk difference for one or more major complications and 95% CI, and linear regression for length of stay, physical function, and blood tests.

We will perform an intention-to-treat analysis. However, since investigators can decide to withdraw a subject from the study for life-threatening medical reasons (see the subsequent section on Recruitment, consent, and withdrawal), we will perform an additional per protocol analysis and compare baseline characteristics of patients withdrawn and patients lost to follow-up. We will use multiple imputation to account for missing variables.

We will perform an interim analysis when 40 patients are randomized. If we find a significant difference through Fisher’s exact test in patients having one or more major or minor complications, we will terminate the trial. Based on previous studies, we will test our final non-inferiority hypothesis without alpha adjustment for the superiority tested interim analysis.

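### The primary outcome is defined in two incompatible ways: one leaves out partial flap loss that needs a second free flap, the other counts it, and the non-inferiority verdict can turn on which is used

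*Protocol article*

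**What the plan says.** The protocol article describes the primary outcome in several places.

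- **Objectives, outcome sentence:** the outcome is the "proportion of patients who experienced partial flap loss which did not require another free flap procedure". This is minor loss only.
- **Objectives, end of the same paragraph:** "We will calculate the absolute risk differences in incidence of partial flap loss (major and minor combined) between groups".
- **Statistical analysis, first sentence:** "As the primary hypothesis we will calculate the absolute risk differences in incidence of partial flap loss (major and minor combined) between groups". Non-inferiority is concluded if the upper limit of the 95% confidence interval stays within 12%.
- **Study parameters, meaning of the terms:** "Partial flap loss is defined as a minor complication if no secondary free flap is needed", and it counts "as a major complication if a secondary free flap was needed".
- **Abstract (Methods), the primary study parameter under Study parameters, and Sample size calculation:** these speak of partial flap loss with no restriction. The 6% planning rate is not tied to either definition.

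**The concern.** Study parameters settles what major and minor mean, so the two statements cannot both be the primary outcome. A patient whose partial loss was bad enough to need another free flap is a non-event under the outcome sentence and an event under the analysis sentences.

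The direction of the error matters in a non-inferiority trial. Under the minor-only definition, a regimen that shifts losses from minor to major lowers its own event rate and looks better. Even if the major share is the same in both arms, removing those events shrinks the absolute difference, which makes it easier to stay inside a fixed 12-point margin. The trial is unblinded, so two definitions on record leave room to choose between them once results are visible.

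**Working it through.** **1. The plan's own sample size**

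Inputs from Sample size calculation: 6% rate, taken as equal in both arms; margin 12 points; 80% power; two-sided 95% interval (one-sided 0.025); 5% loss to follow-up. The allocation ratio is not stated, so 1:1 is assumed.

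n per arm = (1.960 + 0.842)² × 2 × 0.06 × 0.94 / 0.12² = 61.5, rounded up to 62.

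Total 124, and 124 / 0.95 = 131 after rounding up. The article states 130, so its figure is reproduced. The problem lies in the definition, not in this arithmetic.

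**2. Sensitivity of the verdict to single events**

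With 62 analysed per arm, one event is 1/62 = 1.6 points. The Wald upper limit is d + 1.96 × √[p_B(1−p_B)/62 + p_A(1−p_A)/62]. The counts below are assumed, with 3 events in group A (dangling).

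| Events in B | Difference | Wald upper limit | Newcombe upper limit |
|---|---|---|---|
| 4 | 1.6 | 9.7 | 11.2 |
| 5 | 3.2 | 11.9 | 13.2 |
| 6 | 4.8 | 13.9 | 15.2 |

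Suppose the minor-only counts are 4 (B) against 3 (A). Non-inferiority is declared. Two further losses in B that needed a second flap make it 6 against 3, and non-inferiority is not shown under either interval. One such loss is enough to change the verdict under Newcombe.

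**3. Chance of declaring non-inferiority when the combined outcome sits at the margin**

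Take true combined rates of 6% (A) and 18% (B), which differ by exactly 12 points. Let s_A and s_B be the shares of partial losses that need a second flap. The minor-only rates are 0.06 × (1 − s_A) and 0.18 × (1 − s_B). Exact enumeration of both binomial distributions, with 62 per arm, gives:

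| s_A, s_B | Minor-only rates A, B | Difference (points) | Wald | Newcombe |
|---|---|---|---|---|
| 0, 0 (same as combined) | 6.0%, 18.0% | 12.0 | 3.6% | 2.5% |
| 5%, 5% | 5.7%, 17.1% | 11.4 | 4.6% | 3.2% |
| 10%, 10% | 5.4%, 16.2% | 10.8 | 6.0% | 4.0% |
| 25%, 25% | 4.5%, 13.5% | 9.0 | 12.4% | 7.8% |
| 25%, 50% | 4.5%, 9.0% | 4.5 | 44.7% | 32.2% |

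The last row is a deliberately adverse case in which the experimental arm also makes losses more severe. The article does not split partial loss into major and minor, so every share is an assumption.

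**4. Effect on the planning rate**

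Power with 62 per arm is Φ(0.12 / √[2p(1−p)/62] − 1.96). It is 80% at p = 6%. If 6% is the minor-only rate and the combined rate is 8%, 10% or 12% (assumed), power falls to 69%, 61% or 54%. The total needed, with 5% loss, rises to 171, 209 or 245. If 6% is the combined rate, the planned 130 stands for the combined outcome.

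**The case against.** The strongest reply is that the two versions do not carry equal weight. The Statistical analysis section is explicit, the end of the Objectives paragraph agrees with it, and the unrestricted wording in the abstract, the primary study parameter and the sample size section is compatible with the combined outcome. Only one clause in one sentence excludes major loss. An analyst who follows the statistical section has a single definition, and a later switch to minor-only would be an open departure from it. This stands, and it is the reason for repairing the outcome sentence rather than the analysis. It does not remove the contradiction, because the minor-only version is the very sentence that announces the primary outcome. Nor is that version an obvious slip: partial losses needing a second flap are counted under major complications, a separate secondary objective, so minor-only is a coherent reading.

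That separate objective also means severe losses would be reported with their own risk difference and interval. This is correct. They would still not enter the non-inferiority decision.

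Third, the two definitions give the same result if no partial loss needs a second flap, and small shares have small effects. This also stands. The verdict can depend on the definition but need not, and the larger error rates above are conditional on the assumed shares.

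That the article condenses a fuller protocol is no answer. This is not an omitted detail but two conflicting statements.

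**Conclusion.** The concern holds. The article gives the primary outcome two incompatible definitions within a single paragraph of Objectives, and no other section reconciles them. As written, the outcome sentence treats the most serious partial losses as non-events.

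The size depends on how many losses need a second flap, which the article does not say. At 62 per arm, one or two such events can reverse the conclusion. When the combined outcome is truly at the margin, the chance of a false non-inferiority claim under minor-only runs from little above nominal at a 5% share to several times nominal at 25%, and far higher if the shares differ between arms. These figures assume 1:1 allocation and 62 analysed per arm.

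Because this is the primary endpoint, it must be settled before analysis.

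**What to change.** In Objectives, delete the clause that restricts the primary outcome to losses not requiring another free flap. Then use one definition throughout: any partial flap loss, major or minor, up to 6 months. This matches the Statistical analysis section as it stands. A minor-only and major-only breakdown may be reported as secondary information.

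In Sample size calculation, state that the 6% refers to the combined outcome. If it proves to be a minor-only rate, recalculate the sample size.

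The cost is one amended sentence and one clarification. Both types of partial loss are already classified under Study parameters, so no new data are needed. Make the change, and date it, before any comparison by arm is seen.

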## Methods/design

### Trial design

The study is taking place at three Dutch hospitals: University Medical Center (UMC) Utrecht, Erasmus University Medical Center (Erasmus MC) Rotterdam, and UMC Groningen. A dangling protocol is the current standard of care in these hospitals. Patients are randomly assigned by a computer program to group A or B. Patients in group A start a dangling protocol on POD 7. Patients in group B can mobilize without limitations starting on POD 7 and are discharged from the hospital when possible. All patients will be seen on POD 12–15, after 5–7 weeks, 2.5–3.5 months, and 5–7 months at the ward or the outpatient clinic. During these visits the complications will be evaluated. The study phases and data collection time points are shown in Fig. 1. The Standard Protocol Items: Recommendations for Interventional Trials (SPIRIT) checklist is provided as Additional file 1.

**Fig. 1 Fig1:**
[figure not shown]
Standard Protocol Items: Recommendations for Interventional Trials (SPIRIT) figure showing the phases of the trial and data collection time points

Patients in group A (dangling) at the UMC Utrecht will undergo blood tests with the use of a point-of-care testing (POCT) device. A drop of blood will be taken on a daily basis from both the flap and from the contralateral leg (control) and will subsequently be analyzed for pO2, pCO2, and pH levels. Moreover, all patients will be asked to fill out three short (PROMIS, EQ-5D, and VAS) online questionnaires at 3 and 6 months and at 1, 1.5, and 2 years postoperative. The inclusion and exclusion criteria are listed in Table 1.

**Table 1 Tab1:** Inclusion and exclusion criteria for “the dangle study”

Inclusion criteria	- Male or female
	- Age between 18 and 99 years old
	- Lower leg defect in need of a free flap reconstruction
Exclusion criteria	- Age under 18 years
	- Co-morbidities that prevent the patient from being able to undergo a dangling protocol
	- Insufficient Dutch language skills to understand the study
	- Patients who are mentally incompetent or are unable to give informed consent
	- Reconstruction with 2 or more free flaps
	- Patients who are getting a secondary free flap due to partial or total free flap necrosis

### Study parameters

As our primary study parameter we will investigate whether there is a significant increase in the incidence of partial flap loss in patients who did not undergo a dangling protocol (group B) versus patients who did undergo a dangling protocol (group A). We defined complete flap necrosis, partial flap necrosis (if a revision surgery with a second free flap is necessary), and pulmonary embolism as major complications. Screening for pulmonary embolism will only be performed if there is a clinical suspicion of a pulmonary embolism. Partial flap loss is defined as a minor complication if no secondary free flap is needed or as a major complication if a secondary free flap was needed. Wound dehiscence, wound infection, failure of skin graft ingrowth on the free flap, and hematoma for which a surgical exploration was needed were defined as minor complications.

### Randomization

Randomization will be performed in Castor EDC, Amsterdam, the Netherlands. This study cannot be blinded. The randomization is stratified per medical center. The coordinating researcher will log in to the computer system and fill out the required information. In case of a re-intervention, the patient will still be included in the study. If the arterial and/or venous anastomosis required a redo, then the day of the performed re-intervention will be POD 0. The study (dangling or no-dangling protocol) will start 7 days after the re-intervention.

In case the patient has a partial or complete flap loss and a secondary free flap transplantation is indicated, the patient will not be re-invited to join the study for randomization after the secondary free flap.

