### Sample size calculation

Based on the incidence of partial flap necrosis in the meta-analysis by Xiong et al., we performed a power calculation [8]. Because total free flap loss rarely occurs after POD 5, we decided to focus in this study on partial flap loss. Based on a rate of partial flap loss of 6%, we decided that an absolute increase in incidence of 12% would be clinically significant. To detect this non-inferiority margin with 80% power and a two-sided 95% confidence interval (CI) and 5% estimated loss to follow-up, we aim to include 130 patients. Each year about a hundred lower limb reconstructions are performed at our three hospitals, resulting in an inclusion time of 2 years.

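### Centre stratifies the randomization but is not carried into the stated analyses; adding it is a nearly free gain in precision, mainly for length of stay and physical function

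*Protocol article*

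**What the plan says.** On design, the Protocol article states under Trial design that "The study is taking place at three Dutch hospitals", and under Randomization that "The randomization is stratified per medical center". Centre is the only stratification factor named.

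On analysis, the Statistical analysis section defines the primary comparison: "As the primary hypothesis we will calculate the absolute risk differences in incidence of partial flap loss (major and minor combined) between groups". The decision rule is: "If the upper limit of the 95% CI falls within 12%, we regard this as a non-inferiority difference". For secondary outcomes it gives "absolute risk difference for one or more major complications and 95% CI, and linear regression for length of stay, physical function, and blood tests". The same section also sets the analysis sets, multiple imputation, the interim test (Fisher's exact) and the position on alpha. Centre is not mentioned in it. No covariates are listed for the regressions, none are excluded, and nothing is described as unadjusted.

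**The concern.** When allocation is balanced within centres, chance imbalance between centres is largely removed by design. A standard error that ignores centre still counts between-centre variation as noise. Where centres differ on the outcome, the resulting interval is therefore somewhat wider than the design warrants.

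Two things could be at stake. The primary conclusion rests on a single upper confidence limit against 12 percentage points, so needless width works against a non-inferiority claim. Length of stay is the benefit that the article hopes to show for the no-dangling group, and a continuous outcome can lose more precision than a rare binary one if hospitals differ. The Limitations section says that a materially larger sample would not be feasible, so precision available from data already collected is worth taking.

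**Working it through.** **Inputs from the article:** partial flap loss 6% and margin 12 points ("Based on a rate of partial flap loss of 6%, we decided that an absolute increase in incidence of 12% would be clinically significant"); 80% power; two-sided 95% interval; 5% loss to follow-up; N = 130; three centres.

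**Assumptions:** 1:1 allocation; the same centre rates in both arms when computing power; centre rates averaging 6%, from 6/6/6% to 1/2/15%; centre explaining 2% to 20% of the variance of a continuous outcome. The article gives no centre-specific figures.

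**Step 1. Reproduce the stated N.** Per arm, n = 2p(1−p)(z₀.₉₇₅ + z₀.₈₀)²/δ² = 2 × 0.06 × 0.94 × (1.960 + 0.842)²/0.12² = 0.1128 × 7.849/0.0144 = 61.5, so 62 per arm and 124 evaluable. Then 124/0.95 = 130.5, rounded up to 131, which agrees with 130 to within one patient. The formula has no centre term, so N does not rely on stratifying.

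**Step 2. Primary outcome, analytic.** With equal-sized centres, the ratio of stratified to crude standard error (SE) is √[mean of p_c(1−p_c) / p̄(1−p̄)], with p̄(1−p̄) = 0.0564. For 1/2/15%, the mean is (0.0099 + 0.0196 + 0.1275)/3 = 0.0523, and √(0.0523/0.0564) = 0.963. With V the variance term, SE = √(2V/62) and power = Φ(0.12/SE − 1.96).

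| Assumed centre rates | SE ratio | Nominal power | n per arm |
|---|---|---|---|
| 6/6/6% | 1.000 | 80.3% | 61.5 |
| 3/6/9% | 0.995 | 80.7% | 60.8 |
| 2/4/12% | 0.983 | 81.6% | 59.4 |
| 1/2/15% | 0.963 | 83.2% | 57.0 |

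The crude value is 80.3% in every row. In interval terms, the crude half-width is 1.96 × 0.0427 = 8.4 points, and the most extreme scenario reduces it to 1.96 × 0.0411 = 8.1 points.

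**Step 3. Primary outcome, simulated.** There were 200,000 runs per scenario with 62 per arm. A crude Wald interval was compared with a size-weighted stratified interval (n−1 variances). With near-equal centres, crude versus stratified power was 81.9 vs 81.6%, 82.4 vs 82.3%, 82.9 vs 82.9% and 83.7 vs 84.0% for the four scenarios in order. With unequal centres (31, 21 and 10 per arm), stratifying changed power by between −0.7 and +0.4 points. When the true difference equalled the margin (near-equal centres), non-inferiority was claimed in 3.4 to 3.7% of crude runs and 3.5 to 3.6% of stratified runs. Both exceed the nominal 2.5% because Wald intervals behave poorly with few events, so that excess is not caused by leaving centre out.

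**Step 4. Length of stay and physical function.** If centre explains a share R² of the outcome variance, adjustment multiplies the SE by √(1−R²), and effective N rises by 1/(1−R²) − 1.

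| R² (assumed) | SE ratio | Effective-N gain |
|---|---|---|
| 2% | 0.990 | 2% |
| 5% | 0.975 | 5% |
| 10% | 0.949 | 11% |
| 20% | 0.894 | 25% |

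**Step 5. Sparse cells.** At 6%, 124 patients yield 124 × 0.06 = 7.4 events, or about 1.2 in each of the six centre-by-arm cells. A cell of 21 patients has no event with probability 0.94²¹ = 0.27.

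**Step 6. Scope.** Under Point-of-care blood tests, samples come only from group A at one hospital. There is no between-arm contrast and no centre factor, so that regression drops out of the point.

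**The case against.** The strongest objection is that this rests on silence. A reader might infer that the article commits to crude comparisons, perhaps because the interim Fisher's test and the sample size formula both ignore centre. The documents do not support that. A Mantel-Haenszel risk difference is also an absolute risk difference between groups, and linear regression accepts centre as a term. The article condenses a fuller protocol (version 7.0), which is not shown and may already specify centre. This part of the objection stands, so the point holds only conditionally: if centre is left out, some precision is lost.

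A reader might also infer that the non-inferiority test is compromised or short of power. It is not. Excess width is conservative for a non-inferiority claim, and Steps 2 and 3 show next to no gain on the primary outcome, with a slight loss in some scenarios. With about one event per cell, a stratified interval is not clearly better for power.

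Finally, a reader might take it as given that discharge practice differs between the hospitals. The article says nothing of the kind. It says only that dangling is standard care at all three, and that discharge depends on clinical judgement. Centre differences in length of stay are plausible but assumed, which is why a range is shown.

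What survives is narrower. The section goes into real detail on the analysis yet omits the only design stratum, and adding it uses data already recorded.

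**Conclusion.** The point holds as a low-severity precision improvement. The design stratifies by centre, and the stated analyses do not mention it. For the primary outcome, stratifying reduces the standard error by 0 to 4% over the assumed centre rates and leaves simulated power essentially unchanged. The reason to do it there is consistency with the design. For length of stay and physical function the reduction is about 1% to 11%, and where it falls depends wholly on how much variance centre explains, which the article does not give. Neither the sample size nor the validity of the non-inferiority test is affected.

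Settling the matter in advance has one further benefit. The trial is unblinded, and a stated choice prevents crude and adjusted limits from being compared before one is picked.

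**What to change.** Add one sentence to the Statistical analysis section, or confirm that the full protocol already has it:

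- The regressions for length of stay and physical function include centre as a fixed effect.
- The risk differences, for partial flap loss and for major complications, are centre-stratified, for example with Mantel-Haenszel weights and an interval suited to sparse strata.
- The unstratified risk difference is reported as a sensitivity analysis.
- The blood-test regression is left as it is.

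The cost is the sentence itself. Centre is already recorded, and no change to sample size, data collection or margin is needed. The one drawback is sparse centre-by-arm cells for the primary outcome, so the interval method should be named together with the weights.

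### A fully salvaged anastomotic redo under the allocated regimen is no event in the complication or interim comparisons, and the rules for such a patient are not reconciled

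*Protocol article*

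**What the plan says.** All references are to the protocol article.

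- **Randomization.** "In case of a re-intervention, the patient will still be included in the study". For the anastomosis in particular: "If the arterial and/or venous anastomosis required a redo, then the day of the performed re-intervention will be POD 0", and "The study (dangling or no-dangling protocol) will start 7 days after the re-intervention". The section does not separate a redo before the regimen from a redo during it.
- **Study parameters.** "We defined complete flap necrosis, partial flap necrosis (if a revision surgery with a second free flap is necessary), and pulmonary embolism as major complications". The minor complications are partial flap loss that needs no second free flap, together with "Wound dehiscence, wound infection, failure of skin graft ingrowth on the free flap, and hematoma for which a surgical exploration was needed".
- **Statistical analysis and Objectives.** For the primary hypothesis, "we will calculate the absolute risk differences in incidence of partial flap loss (major and minor combined) between groups". Major and minor complications are secondary comparisons. An interim analysis at 40 randomized patients applies Fisher's exact test to patients with any major or minor complication, and a significant difference ends the trial. The main analysis is by intention to treat.
- **Recruitment, consent, and withdrawal.** If an adverse event stops a patient from carrying out either regimen adequately, that patient leaves the study for the primary outcome and stays, where possible, for the secondary objectives.
- **Background.** Patients dangle the leg "in order to gradually subject the free flap to increased venous pressure resulting from gravitational forces".

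**The concern.** The trial asks whether graded dangling can be omitted safely. The rationale for dangling is that it brings the flap to venous pressure in steps; group B may let the leg hang without limit from POD 7. Venous compromise that needs a redo of the anastomosis therefore lies on the harm pathway that the trial sets out to examine. The plan foresees the redo by name but uses it only to move the clock. It is not a complication, while surgical exploration for a hematoma is.

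Two things are at stake. If redos under the regimen are commoner in one arm and the flaps are saved, the secondary safety comparisons and the interim stopping rule will not register the difference. And because two sections give different instructions for a patient with an event under the regimen, such patients could be handled differently between centers.

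**Working it through.** **1. The plan's own figure, used here only for the denominator.** Inputs from Sample size calculation: 6% in both arms, 12% margin, 80% power, two-sided 95% interval, 5% loss. Allocation is not stated; 1:1 is assumed.

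n per arm = 2 × 0.06 × 0.94 × (1.960 + 0.842)² / 0.12² = 61.48, rounded up to 62. Total with loss = 2 × 61.48 / 0.95 = 129.4, rounded up to 130. The stated 130 reproduces. Evaluable per arm = 130 × 0.95 / 2 = 61.75, about 62.

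**2. Where a redo under the regimen would count.**

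| Comparison | What counts | Redo, flap fully saved | Redo with a listed sequel |
|---|---|---|---|
| Primary | Partial flap loss | No event, and rightly so | Event if partial loss |
| Major complications | Complete necrosis, partial necrosis needing a second free flap, pulmonary embolism | No event | Event if one of these |
| Minor complications | Other partial loss, dehiscence, infection, graft failure, explored hematoma | No event | Event if one of these |
| Interim stopping test | Any major or minor complication | No event | Event |

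The gap is the third column, in the last three rows.

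**3. The two rules side by side, for a redo after the regimen has started.**

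- Randomization: the patient stays in, the day of the redo becomes POD 0, and the regimen begins 7 days later. No time limit is given.
- Recruitment, consent, and withdrawal: if the event prevents the regimen, the patient is taken out for the primary outcome.

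The article does not say which rule governs. Under either one, the redo itself is not an event.

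**4. Scale.** The documents give no redo rate. Assume 2% to 5% after the start of the regimen:

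- final analysis: 0.02 × 62 = 1.2 to 0.05 × 62 = 3.1 patients per arm;
- interim, 40 / 2 = 20 per arm: 0.02 × 20 = 0.4 to 0.05 × 20 = 1.0 patient per arm.

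One patient can matter at the interim look. As a hypothetical example, take 20 per arm and a two-sided 0.05 level (the article says only that the difference must be significant):

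- 0 against 4 patients with a complication: p = 2 × C(20,4) / C(40,4) = 2 × 4,845 / 91,390 = 0.106;
- 0 against 5, with one redo added to the arm that has 4: p = 2 × C(20,5) / C(40,5) = 2 × 15,504 / 658,008 = 0.047.

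This shows how sensitive a test on 40 patients is to the definition. It does not predict what will happen.

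**The case against.** The strongest reply is that the POD 0 rule is meant for early redos. The text speaks of a study that will start, not start again. It stands under Randomization, patients are invited before POD 5, and the regimens begin on POD 7. Read so, the rule only ensures that every patient begins 7 days after a working anastomosis. This reading fits at least as well as any other, so it should not be claimed that the plan resets the clock after the regimens have begun. What stands is that the text sets no limit. The gap in the complication lists does not depend on the point.

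The second reply is that a salvaged flap is by definition not partial flap loss. That is right, and the primary outcome definition needs no change on this account.

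The third is that serious adverse events by arm are commonly left to the full protocol. That is fair for reporting in general. Here, however, the article states the complication lists, and the interim stopping rule uses them.

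A reader might also infer stronger claims that the documents do not support:

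- **That a redo leaves no trace.** Any partial loss, graft failure, dehiscence, infection or explored hematoma that follows still counts, and a redo may show in length of stay and costs, though these are not safety outcomes.
- **That hospital days are lost.** Nothing says that length of stay is counted from the new POD 0.
- **That the hidden harm can be set against the 12-point margin.** That margin was set for partial flap loss, so the comparison mixes endpoints, and the redo rate is assumed.
- **That the bias must favor non-inferiority.** Group A dangles too, so redos can occur in both arms, and the Background says that the protective effect of dangling lacks evidence.

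**Conclusion.** The point holds in a limited form. As the complications are defined, a redo of the anastomosis that occurs under the allocated regimen and is fully salvaged is not an event in the major, minor or interim stopping comparisons, although it is a plausible harm of the regimen and a hematoma needing exploration does count. The reach of the POD 0 rule in time is open, and for an event under the regimen it is not reconciled with the withdrawal rule.

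The likely size is small in absolute numbers: 1 to 3 patients per arm at the end and up to one per arm at the interim look, if 2% to 5% is a fair guess and allocation is 1:1. The direction is unknown. The sample size and the primary outcome definition are unaffected. This is a cheap improvement to the safety comparison, not an error in the primary analysis.

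**What to change.** 1. In Study parameters, add redo of the arterial or venous anastomosis after the start of the allocated regimen to the complications, so that it enters the secondary and interim comparisons. Report the number by arm.
2. For outcome assessment of such patients under intention to treat, keep the day on which the allocated regimen first started as the anchor, so that a new POD 0 does not shift their outcome windows.
3. State whether the POD 0 rule covers a redo after the regimen has begun, and reconcile the Randomization section with the Recruitment, consent, and withdrawal section on whether the patient stays in the primary outcome. How the patient is managed clinically after a redo is for the sponsor to settle.

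The cost is a short amendment. Redos should already be in the operative record, so little or no new data collection is expected. The downside is a somewhat higher complication rate. The change to the interim endpoint should be made without sight of results by arm.
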